### Secondary objectives

To quantify and draw inferences on observed differences in the VISA-A score at 3-month post-randomisation.To identify any differences in health-related quality of life measurement (HRQoL) between trial treatment groups at 3-month and 6-month post-randomisation.To identify any differences in pain measurements between trial treatment groups at 2-week, 3-month and 6-month post-randomisation.To report the complication profile of PRP injections at 2-week, 3-month and 6-month post-randomisation.

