### Post-randomisation withdrawals

Participants may withdraw from the trial treatment and/or the trial at any time without prejudice. Unless a participant explicitly withdraws their consent, they will be followed-up wherever possible and data collected as per the protocol until the end of the trial. For participants explicitly withdrawing consent for follow-up procedures, trial data obtained up until the point of withdrawal will be included in the final analysis.

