#### Technical failure

In the unlikely event that the project specific centrifuge system fails once blood has been drawn for PRP preparation/Placebo preparation the patient will be allocated to the placebo arm and analysed as a protocol violation.

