### Statistical methods

The primary analysis will compare the VISA-A score at 6-month follow-up between the two treatment groups on an intention-to-treat (ITT) basis. Mixed-effects linear regression will be used with adjustment for design factors (centre and laterality), age, sex and baseline VISA-A score. Centre will be taken as a random effect to allow for possible heterogeneity in patient outcomes. Mean difference with 95% CI will be reported. Data transformation will be applied to the outcome before the modelling if VISA-A at 6 months is non-normally distributed. A p value<0.05 will be considered statistically significant.

The secondary analysis compares the outcomes including VISA-A at 3 months, EQ-5D-5L VAS and index scores at 3 and 6 months and pain VAS and complication rate at 2 weeks, 3 and 6 months. They will be analysed by ITT using linear regression with and without adjustment for design factors and baseline data. In addition, VISA-A at 6 months will be analysed in the following ways: (1) unadjusted linear regression by ITT and (2) adjusted mixed-effects regression by per-protocol to assess the impact of non-compliance. Kaplan Meier plot will be used to compare the time to complication by treatment if sufficient number is observed in each complication class. In case of bilateral tendinopathy (both sides), one randomly select side will be included in the analysis. Although missing data are not expected to be a problem for this study, the missing mechanism will be assessed and imputation may be used when deemed appropriate. The imputed data will be used for a sensitivity analysis. Pre-specified subgroup analysis include laterality (single vs bilateral) and duration of symptom (≤median vs>median duration). The analysis will be adjusted in the same way as the primary analysis. A detailed analysis plan will be finalised prior to final data lock.

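### ITT is the only stated analysis set for complications, although the objective concerns PRP injections and some participants allocated to PRP may not receive one; a summary by injection received should be added

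*Protocol article*

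**What the plan says.** All references are to the protocol article.

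- **Objective.** Secondary objectives includes: "To report the complication profile of PRP injections at 2-week, 3-month and 6-month post-randomisation".
- **Analysis set.** Statistical methods lists "pain VAS and complication rate at 2 weeks, 3 and 6 months" among the secondary outcomes and continues: "They will be analysed by ITT using linear regression with and without adjustment for design factors and baseline data".
- **Only non-ITT analysis.** This is "adjusted mixed-effects regression by per-protocol to assess the impact of non-compliance". It is introduced by "In addition, VISA-A at 6 months will be analysed in the following ways", so it does not extend to complications.
- **Other complication analysis.** "Kaplan Meier plot will be used to compare the time to complication by treatment if sufficient number is observed in each complication class". This is conditional on numbers, and it does not say whether treatment means allocated or received.
- **Routes to not receiving PRP.** Under Pre-injection, blood is drawn after randomisation. Under Technical failure, if the centrifuge fails once blood has been drawn, "the patient will be allocated to the placebo arm and analysed as a protocol violation". Under Post-randomisation withdrawals, "Participants may withdraw from the trial treatment and/or the trial at any time without prejudice", and follow-up continues unless consent is explicitly withdrawn.

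**The concern.** The complication profile of an injection describes what follows when that injection is given. Under ITT, a participant allocated to PRP who has the placebo injection or none stays in the PRP denominator, and any complication that person has counts as a PRP complication. For VISA-A, keeping such people in is the cautious choice, because it works against a claim of benefit. For harms the same rule leans the other way, towards no difference. The article checks the effect of non-compliance on the primary outcome but states no matching check for complications.

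Centrifuge failure acts in one direction only: a PRP participant moves to placebo, while a placebo participant stays on placebo. At stake is whether the complication table can be read as describing PRP injections, in a trial meant to inform practice and policy.

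A second difficulty is that the Technical failure wording does not sit cleanly with ITT. Two analysts following the article could place the same participant's complication in different arms.

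**Working it through.** **Figures in the article.** The article gives no complication rate and no expected share of participants who will not receive PRP. The only figure used here is the sample size, and it reproduces. With a difference of 12, an SD of 26, 5% two-sided (sidedness assumed) and 90% power, 2 × (1.960 + 1.282)² × 26² / 12² gives 99 per group (99.6, so 100, with the t distribution). Then 200 / 0.85 gives 236, close to the stated 240. At 1:1 that is 120 per arm. The point below does not affect the sample size.

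**Formula.** Let p1 be the complication rate after a PRP injection, p0 the rate after a placebo injection, and x the share of the PRP arm that does not receive PRP. Assume that nobody allocated to placebo receives PRP and that not receiving PRP is unrelated to risk. For those given the placebo injection instead:

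- ITT rate in the PRP arm = (1 − x) p1 + x p0
- ITT risk difference = (1 − x)(p1 − p0)

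Participants who receive no injection also lack the PRP-specific excess, so that component shrinks by the same factor.

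**Illustration.** All rates and values of x are assumptions. The half-width is 1.96 × √[p1(1 − p1)/120 + p0(1 − p0)/120].

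| p1 v p0 | Difference as received (points) | x = 2% | x = 5% | x = 10% | x = 20% | 95% CI half-width (points) |
|---|---|---|---|---|---|---|
| 20% v 5% | 15.0 | 14.7 | 14.25 | 13.5 | 12.0 | 8.2 |
| 20% v 10% | 10.0 | 9.8 | 9.5 | 9.0 | 8.0 | 8.9 |
| 5% v 1% | 4.0 | 3.92 | 3.80 | 3.60 | 3.20 | 4.3 |

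For the first row, √(0.16/120 + 0.0475/120) = 0.0416, and 1.96 × 0.0416 = 0.082. Of 120 participants, x = 2%, 5% and 10% correspond to about 2, 6 and 12 people. At 20% v 10%, power with 120 per arm falls from 0.58 to 0.57, 0.55 and 0.51 for x = 2%, 5% and 10%.

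**Events outside the formula.** The Secondary outcome section lists bruising and discomfort at the venesection site, and fainting associated with venesection or tendon injection. Blood is drawn in both arms before the injection, so the rate of venesection events does not depend on which injection follows.

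**The other reading of Technical failure.** Suppose technical failures are counted as placebo, and let x here be their share alone. The PRP arm then has 120(1 − x) people, all at p1, and the placebo arm has 120(1 + x), all at p0. The difference is p1 − p0, with no dilution by this route, but the comparison is no longer by randomised group. The article does not say which reading applies.

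**The case against.** The strongest reply is about size. Treatment is a single injection given after randomisation, and the article calls centrifuge failure unlikely. For x up to 10%, the shift is 0.3 to 1.5 points at 20% v 5%, against a half-width of 8.2. At 5% v 1% it is about 0.1 to 0.4 points, against 4.3. No plausible conclusion turns on that. Nor do rare classes such as infection rescue a stronger case: at a 1% rate, 2 to 12 people yield only 0.02 to 0.12 expected events. This stands, and it limits how much weight the point can bear.

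It can also be said that centrifuge failures might be counted as placebo. This stands too. A reader might infer that they certainly enter the PRP denominator. Strict ITT would put them there, but the Technical failure wording leaves the matter open.

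A third reply is that a supplementary safety set is usually left to the detailed analysis plan, which the article promises before data lock, and that the data monitoring committee reviews compliance and safety. A later plan could indeed add such a set. However, the article is not silent here: it names ITT for complications and confines its one alternative analysis to VISA-A. That is a stated rule which does not fully serve its own objective.

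Finally, making the as-received table the main one would displace the randomised comparison. If it were limited to injected participants, it would also omit someone who fainted at the blood draw and was never injected. This stands, and it shapes the fix.

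**Conclusion.** The point holds as a modest one. ITT is the only analysis set the article states for the complication rate, and it pulls any excess caused by the PRP injection itself towards zero by the factor (1 − x). The direction follows from the formula, given that no placebo participant receives PRP and that not receiving PRP is unrelated to risk. The size cannot be established, because neither x nor the rates are given. It is probably small, and it is zero if everyone allocated to PRP receives it. The arm in which technical failures are counted is unresolved between Technical failure and Statistical methods.

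A reader might infer that the safety objective is answered for the wrong group, or that added harm would be hidden. The article does not support either inference: under the assumed rates and x up to 10%, the shift lies well inside the sampling uncertainty, venesection events are unaffected, and the ITT comparison remains a valid randomised contrast. This is a cheap improvement, not a flaw that threatens the trial's conclusions.

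**What to change.** In Statistical methods, keep the ITT comparison of complications and add one pre-specified summary by injection actually received, in three groups: PRP, placebo and none. Events in participants who had venesection but no injection belong in the third group, so that nothing is dropped. State whether the Kaplan-Meier plot is by allocated or received treatment.

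Reconcile Technical failure with Statistical methods by saying in which arm these participants are counted in the ITT analysis and what being analysed as a protocol violation means there. Settle this before data lock, so that the grouping is not chosen after events have been seen.

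The cost is a few sentences and one extra table. It needs the injection given to be recorded for each participant, which is a reasonable expectation although the article does not state it. The downside is that the received-treatment groups are not strictly randomised, which is why the ITT comparison stays beside them.

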### Screening and eligibility

Eligible patients will be identified from foot and ankle clinics by the local principal investigator (PI) and invited to speak to a suitably qualified member of the research team. The research team member will complete the eligibility checklist in conjunction with a suitably qualified member of the clinical team. Screening logs will be collected by the clinical care team in a minimum of 20 National Health Service trusts in the UK to assess the main reasons for patient exclusion as well as the number of patients willing to take part.

Patients will be provided with verbal and written information about the study. Written informed consent will be obtained (online supplementary file 3) by a suitably qualified member of the research team, after allowing sufficient time for the patient to consider their decision and ask questions about the trial.

10.1136/bmjopen-2019-034076.supp3Supplementary data

Patients aged 18 years or over with pain at the mid-substance of the Achilles tendon for longer than 3 months confirmed by ultrasound and/or MRI are eligible for the trial. Patients will be excluded for the following reasons: (i) if there is presence of a systemic conditions (including diabetes, rheumatoid arthritis, peripheral vascular disease), (ii) if they are unable to adhere to trial procedures, are pregnant or actively trying to become pregnant or breastfeeding at the time of randomisation, (iii) if they have had prior Achilles tendon surgery or rupture on the index side, have had previous major tendon or ankle injury or deformity to either lower leg, (iv) if they have had a fracture of a long bone in either lower limb in the previous 6 months, (v) if they have previously been randomised in the study, (vi) if they have previously had PRP treatment into a tendon or have any contraindication to receiving a PRP injection (haemodynamic instability, platelet dysfunction syndrome, active cancer, septicaemia, systemic use of anticoagulant therapy (eg, warfarin, dabigatran, heparin), local infection at site of the procedure). Low dose aspirin use (or equivalent) is not a contraindication to receiving a PRP injection; therefore, these patients will not be excluded from the study.

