Patients presenting with bilateral Achilles tendinopathy will be randomised and treated as one unit, that is, the patient will be randomised rather than the tendon. However an index tendon will be identified (this will be the one the patient perceives to be more severe at the point of randomisation).

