#### Bilateral presentations

The index tendon will be randomised and managed accordingly. Regarding the non-index tendon the participant will have two options, to have no treatment or to receive a second injection into the non-index tendon.

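### In bilateral patients the analysed side is drawn at random, although the trial fixes an index tendon and lets the other tendon go uninjected

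*Protocol article*

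**What the plan says.** The protocol article deals with bilateral disease in three places.

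- **Screening and eligibility.** A bilateral patient is one unit: "the patient will be randomised rather than the tendon". Within that unit "an index tendon will be identified (this will be the one the patient perceives to be more severe at the point of randomisation".
- **Bilateral presentations** (under Interventions). "The index tendon will be randomised and managed accordingly". For the other side: "Regarding the non-index tendon the participant will have two options, to have no treatment or to receive a second injection into the non-index tendon". The type of that second injection is not stated.
- **Statistical methods.** "In case of bilateral tendinopathy (both sides), one randomly select side will be included in the analysis". The sentence stands in the paragraph on secondary analyses. That paragraph also covers further analyses of 6-month VISA-A, missing data and the subgroups by laterality and symptom duration.

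The paragraph on the primary analysis says "The primary analysis will compare the VISA-A score at 6-month follow-up between the two treatment groups on an intention-to-treat (ITT) basis". It adjusts for baseline VISA-A and laterality, among other factors, but does not say which side is analysed in a bilateral patient. The index tendon is not mentioned anywhere in Statistical methods.

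**The concern.** The design singles out one tendon before treatment and attaches the allocation to it. The analysis rule then ignores that choice. Nothing limits the random draw to injected tendons, so a patient allocated to PRP can be represented by a tendon that received nothing.

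The research question concerns PRP placed in the tendon. A tendon that was not injected cannot show that local effect, and including such tendons pulls the difference between arms towards zero. Intention-to-treat does not require this: analysing the index tendon also keeps every randomised patient in the allocated arm.

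The attenuation falls wholly on the bilateral stratum. It would therefore weigh most on the pre-specified laterality subgroup, where it could look like a true difference in treatment effect between unilateral and bilateral disease.

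**Working it through.** **1. The plan's own figure.** Inputs from Sample size: difference 12 points, SD 26, significance level 5% (taken as two-sided), power 90%.

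- n per group = 2 × (1.960 + 1.282)² × 26² / 12² = 98.65, so 99. The t-test version gives 99.6, so 100, as stated.
- Standard error at 100 per group = 26 × √(2/100) = 3.677. Power = Φ(12/3.677 − 1.960) = Φ(1.304) = 0.904 (t-test 0.901).
- 200/0.85 gives 236. The stated total of 240 corresponds to 16.7% loss, which fits the article's approximate 15%.

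The planned size reproduces.

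**2. Share of uninjected tendons in the analysis.** Two quantities are needed that the article does not give:

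- b = share of randomised patients who are bilateral;
- u = share of bilateral patients whose non-index tendon is not injected.

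If the random draw gives each side an equal chance, the share of analysed tendons that were not injected is 0.5 × b × u in each arm.

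**3. Expected difference and power.** Further assumptions: VISA-A is scored per side, an uninjected tendon shows no treatment effect, a second injection (where given) has the same effect as the allocated one, and the SD stays at 26 with 100 analysed per group. Then

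expected difference = 12 × (1 − 0.5 × b × u), and power = Φ(difference/3.677 − 1.960).

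| b | u | uninjected share | difference (points) | power |
|---|---|---|---|---|
| 0%, or any b with u = 0% | – | 0% | 12.0 | 90.4% |
| 10% | 25% | 1.25% | 11.85 | 89.7% |
| 10% | 50% | 2.5% | 11.7 | 88.9% |
| 20% | 50% | 5% | 11.4 | 87.3% |
| 30% | 50% | 7.5% | 11.1 | 85.5% |
| 30% | 100% | 15% | 10.2 | 79.2% |
| 50% | 100% | 25% | 9.0 | 68.7% |

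Worked row, b = 20% and u = 50%: 0.5 × 0.20 × 0.50 = 0.05; 12 × 0.95 = 11.4; 11.4/3.677 − 1.960 = 1.140; Φ = 0.873.

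**4. Laterality subgroup.** Among bilateral patients b = 1, so the expected difference is 12 × (1 − 0.5 × u): 9 points at u = 50% and 6 points at u = 100%. With the same 12-point effect in every injected tendon, the subgroup contrast would show a gap of 3 to 6 points produced by the side rule alone.

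**5. If scoring is not per side.** Outcome measures describes VISA-A as an eight-question patient-reported score and pain as a single line, without saying that either is completed for each leg. With one score per patient, or one for the index side only, there is no second score to draw. Steps 2 to 4 then do not apply, and the sentence describes an analysis that cannot be done.

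**The case against.** Four objections have weight.

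- **Place of the sentence.** It stands among the secondary analyses, so its application to the primary analysis is inferred. That is fair: the reading is reasonable, not explicit. But the wording carries no restriction and no other bilateral rule exists. On the narrow reading, the re-analyses of 6-month VISA-A and the subgroups are still affected, and could rest on a different tendon from the primary analysis.
- **Per-side scoring is not established.** This stands. Attenuation is conditional on it. Without it the defect is an unworkable rule and no power is lost.
- **The size rests on assumptions.** This also stands. The larger losses need every bilateral patient to decline the second injection, and the loss is nil if all accept. The SD of 26 also ignores the adjustment for baseline.
- **A detailed analysis plan is to follow.** That would answer a gap, but here a rule is stated and it conflicts with the design.

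The mismatch over the randomised unit is a lesser matter. Screening and eligibility is explicit that the patient is randomised, and Randomisation agrees, so the phrase about the index tendon being randomised reads as loose wording.

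**Conclusion.** The conflict between the random-side rule and the index-tendon design is certain from the text. Its effect on the result is not. With per-side scoring it attenuates the difference by an amount the article does not allow one to fix: possibly nothing, and 0.6 points and about 3 percentage points of power at 20% bilateral and half uninjected. Without per-side scoring the rule is inoperable. It should be corrected before data lock, but the documents do not show that the primary result is compromised.

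Four stronger inferences are tempting and are not supported.

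- **Selection bias.** A reader might infer it because the patient chooses whether the second tendon is injected. That choice affects the treatment received, not which side is drawn. The draw is random, participants are blinded and laterality is a stratification factor, so the comparison remains randomised.
- **A ceiling effect from milder tendons.** Outcome measures reports no evidence of floor or ceiling effects for VISA-A.
- **Tendons that escaped the exclusions.** The surgery and rupture criterion does name only the index side ("prior Achilles tendon surgery or rupture on the index side"), but the same item also excludes previous major tendon injury in either lower leg.
- **Too small a trial.** The planned size reproduces, and analysing the index tendon leaves it unchanged.

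**What to change.** Replace the sentence in Statistical methods with:

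> *In bilateral cases the index tendon, identified at randomisation before treatment, is the side analysed for baseline and follow-up VISA-A and pain in all primary, secondary and subgroup analyses.*

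Report any non-index data descriptively, if they are collected, according to whether that side was injected. State whether VISA-A and pain are completed per side, for the index side or once per patient, so that the baseline covariate and the follow-up score refer to the same thing. Reconcile the wording on the randomised unit between Screening and eligibility and Bilateral presentations.

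The cost is one replaced sentence and a short clarification. The index side is already identified and the sample size does not change. Whether scores specific to the index side exist must be checked against the questionnaires. The change should be made before the analysis plan is finalised and the data are locked.

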### Sample size

The primary outcome for the study is the VISA-A score^14^; it has a range between 0 and 100, a lower score indicating more symptoms and greater limitation of physical activity and 100 being asymptomatic. The minimum clinically important difference for the VISA-A score is estimated to lie between 10 and 12 points.^11 12^ From our previous feasibility publication,^3^ VISA-A scores were observed to be approximately normally distributed with a SD of 26. If the true difference between the experimental and control treatment group means is 12 points, a sample of 100 patients in each group will be required to reject the null hypothesis (population means of the experimental and control groups are equal) with probability 0.9 (90% power). This equates to an effect size of 0.46, which we would consider to be moderate. The type I error rate (significance level) associated with this test is 5%. Allowing approximately 15% loss to follow-up, this amounts to 240 patients in total.

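### The duration subgroup is fixed as a split at the sample median, which discards information in an already weak comparison; a continuous treatment-by-duration term would be better

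*Protocol article*

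**What the plan says.** The subgroup text in the Protocol article, Statistical methods, is two sentences. The first names the factors and the cut: "Pre-specified subgroup analysis include laterality (single vs bilateral) and duration of symptom (≤median vs>median duration". The second gives the only methodological instruction: "The analysis will be adjusted in the same way as the primary analysis". The primary model in the same section is a mixed-effects linear regression with centre as a random effect and laterality, age, sex and baseline VISA-A as covariates. Symptom duration is not among the covariates.

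Duration of symptoms is listed among the baseline characteristics (Outcome measures), and everyone enrolled must have had pain for more than 3 months (Screening and eligibility). The article gives no reason for cutting at the median. It does not say how effects in the two subgroups will be compared. It defers detail to an analysis plan to be completed before data lock, which is not shown.

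**The concern.** The median split is a choice that the article makes, not a detail left open. It has three drawbacks.

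- The boundary is whatever the recruited sample produces. It cannot be stated in months beforehand and would differ in another cohort, so a finding for the longer-duration half is hard to apply to a patient.
- Two patients just either side of the median are treated as different in kind, while a patient just above it and one with symptoms for many years are treated as alike.
- Dichotomising a continuous modifier loses information, and interaction comparisons in a trial sized for its main effect have little to spare.

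The split also sets up a familiar trap. Two halves invite two p values, and one falling below 0.05 while the other does not is not evidence that the effects differ. How likely that pattern is under a uniform effect is worth knowing before the analysis plan is finalised, because the results are meant to inform practice and policy.

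**Working it through.** **Inputs** (Protocol article, Sample size): "If the true difference between the experimental and control treatment group means is 12 points"; "VISA-A scores were observed to be approximately normally distributed with a SD of 26"; "a sample of 100 patients in each group will be required to reject the null hypothesis", at 90% power and 5% significance (two-sided assumed; this reproduces the stated size); "Allowing approximately 15% loss to follow-up, this amounts to 240 patients in total". Allocation is 1:1 (Abstract).

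**1. The plan's own figure.** n per arm = 2 × (1.960 + 1.282)² × 26² / 12² = 98.7, so 99; the t-test version gives 99.6, so 100. Power at 100 per arm is 90.4%. Then 200 / 0.85 = 235.3, so 236; 240 corresponds to 16.7% loss. The stated size is reproduced.

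**2. Precision between halves.** Take 100 evaluable per arm, so 50 per arm in each half.
- SE of the treatment effect in one half = 26 × √(2/50) = 5.20 points.
- SE of the difference between the two effects = 26 × √(4/50) = 7.35 points.
- Power for a 12-point difference = Φ(12/7.35 − 1.96) = Φ(−0.33) = 37%.
- Difference detectable with 80% power = 7.35 × (1.96 + 0.84) = 20.6 points.

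Baseline adjustment helps somewhat. Multiplying the SE by √(1 − r²), an assumed baseline-outcome correlation r of 0.3 gives 7.35 × 0.954 = 7.02 and power Φ(−0.25) = 40%; r = 0.5 gives 7.35 × 0.866 = 6.37 and power Φ(−0.08) = 47%.

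**3. Cost of the median split.** For a normal covariate, the squared correlation between the covariate and its median-split indicator is 2/π = 0.637. If the interaction is linear in that covariate, the split keeps about 64% of the information; 200 evaluable participants then count as about 200 × 0.637 = 127. In terms of power, a linear interaction that makes the halves differ by 12 points on average has z = 12/7.35 = 1.63 under the split. Analysed continuously, z = 1.63/√0.637 = 2.04, and power is Φ(2.04 − 1.96), about 53% instead of 37% (SD 26, no baseline gain).

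**4. If the halves were tested separately.** Under a uniform 12-point effect, power in each half is Φ(12/5.20 − 1.96) = 63.6%. The chance that exactly one half is significant is 2 × 0.636 × 0.364 = 46.3%. It depends strongly on the conditions:

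| Condition (SD 26, 50 per arm per half unless stated) | Exactly one half significant |
|---|---|
| True effect 0 | 9.5% |
| 3 points | 16% |
| 6 points | 33% |
| 8 points | 45% |
| 10 points | 50% |
| 12 points | 46% |
| 15 points | 29% |
| 20 points | 6% |
| 12 points, r = 0.3 | 44% |
| 12 points, r = 0.5 | 37% |
| 12 points, r = 0.5, 120 evaluable per arm | 28% |

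An interaction test would falsely declare a difference 5% of the time per factor, whatever the size of the uniform effect.

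**The case against.** The split has real merits. It is pre-specified, uses a baseline variable, cannot be tuned to the outcome, gives roughly equal halves and does not inflate the type I error of an interaction test. There are only two subgroup factors, and the primary comparison does not depend on them. The 64% figure needs a linear interaction and a roughly normal (log) duration; the document supports neither, and the entry criterion of more than 3 months truncates the lower end. All of this stands, and it limits the point to a modest improvement. It does not make the median a good cut: even if the true pattern were a threshold, the sample median would match it only by luck.

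A reader might infer more: that the primary model will be re-run in each subgroup with no interaction test, so that a chance result confined to one half is about as likely as not. The document does not support this. The instruction on adjustment concerns covariates. It neither prescribes separate models nor rules out an interaction term. For laterality it fits a model in all participants better, because laterality is constant within each stratum and could not be adjusted for there. For duration it leans the other way, because the primary covariates contain no duration main effect. The wording therefore settles nothing, and naming the test is a detail that an article may leave to the analysis plan. Nor does the article say that within-half p values will be compared. The 46% is conditional on separate testing, a uniform effect near the design value, SD 26 and no gain from baseline adjustment.

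**Conclusion.** The concern holds for the median split of symptom duration. The article fixes a cut that is unknown until recruitment ends and has no stated clinical meaning. If log duration is roughly normal and the interaction linear, the cut gives up about 36% of the information on effect modification. It does so in a comparison with an SE of about 7.4 points and about 37% power for a 12-point difference (40% to 47% with an assumed baseline correlation of 0.3 to 0.5).

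That no interaction test is planned cannot be concluded; the article is silent on it. The discordance figure of about 46% is a reason for the analysis plan to name the interaction as the test. It is not a prediction of what the trial will report. The matter affects secondary, exploratory results only.

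**What to change.** In the analysis plan, replace the duration subgroup wording with text such as: *Modification of the treatment effect by symptom duration will be assessed in all participants by adding a duration main effect and a treatment-by-duration term to the primary model, with duration continuous on the log scale and linearity checked. The interaction estimate and its 95% CI will be reported, with fitted treatment effects at a few fixed durations stated in advance. Effects in the halves below and above the median will be shown for description only. Laterality will be assessed by a treatment-by-laterality term added to the primary model in the same way.*

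The cost is a few sentences and slightly more analysis work, with no new data. The downside is that a functional form for duration must be assumed, which is why the linearity check belongs in the wording. Power for interaction remains limited after the change, so the estimates should be read through their confidence intervals.
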